## SAMPLE SIZE

Refer to Section 5, Statistical Design and Analysis, for more details.

A total of 2,000 children (1,000 per treatment group) will be enrolled. With this sample size we aim to rule out a relative increase in failure rate of 50%. The power of the study to show non-inferiority of the 3-day treatment group at the final analysis when both treatment groups have exactly the same failure rate depends on the failure rate in the standard treatment (5-day) group. The estimated power is adjusted for a 5% loss to follow-up rate in each of the arms. For example, with 1,900 children (950 per treatment arm) for the primary analysis this study has 88% power to show non-inferiority of the 3-day treatment group if the failure rate in both groups is 8% and the non-inferiority margin is a 50% relative increase (which for this failure rate is equivalent to an absolute non-inferiority margin of 4.0%). For this failure rate in the standard treatment group (of 8%), at the final analysis the 95% confidence interval would exclude 12.0%, even if the failure rate is as large as 9.7% in the 3-day treatment group. With 1,900 children with complete outcome data in the primary analysis, the power of this study to show non-inferiority ranges from 64.8% if the failure rates in both groups are 4%, to 96.5% if the failure rates in both groups are 12% (assuming a relative non-inferiority margin of 50% (or equivalently a factor of 1.5). Further details will be provided in the Statistical Analysis Plan (SAP).

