## Randomization

Randomization and enrollment occur at the same study visit, designated Day 1. Randomization is defined as the process of assigning a child to a study arm; assignments are computer-generated by the Protocol Statisticians at UW. The study pharmacists on site will receive the randomization list from the Protocol Statisticians and will be responsible for recording the blinded portion of the randomization code on each study participant’s case report forms and blister pack when they are enrolled and randomized. The list that contains a link between the allocation arm and the study participant ID will be maintained by the study pharmacists under lock and key and/or electronic encryption. Other study staff will not have access to the randomization list.

Children will be randomized to 3 days of oral amoxicillin DT followed by 2 days of placebo DT (intervention) or 5 days of oral amoxicillin DT (control). Treatments will be allocated in a 1:1 ratio. Study investigators and staff will be blinded to all elements of the randomization allocation for the duration of the study.

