  - Any time before or on day 6: WHO IMCI danger signs, severe respiratory distress (e.g., grunting, nasal flaring, head nodding, or severe chest-indrawing), oxygen saturation by pulse oximetry < 90%, missing 3 or more doses due to vomiting, change in antibiotics prescribed by a study clinician, or death.
  - At or after initial hospitalization discharge assessment (between 42 and 60 hours post-enrollment): documented axillary temperature > 38 ºC with chest-indrawing.
  - At day 6 outcome assessment: persistence of chest-indrawing, or axillary temperature > 38 ºC.
  - For the purposes of this protocol, children who do not fail on assessment at day 6 will be considered clinically cured. Loss to follow-up or withdrawal from the study at any time after enrollment and before the day 14 follow-up visit will be considered missing outcome data for that respective time point.
- *Clinical relapse* will be defined as recurrence of signs of chest-indrawing pneumonia, severe respiratory distress (e.g., grunting, nasal flaring, head nodding, or severe chest- indrawing) or severe disease after day 6 among those who did not have treatment failure at or by day 6.

Recruitment and follow-up is expected to continue until the maximum sample size is achieved. For the chest-indrawing pneumonia study a total of 2,000 children (1,000 per treatment group) will be enrolled. We are assuming a treatment failure rate of 8% in the 5-day control group and a relative 1.5 non-inferiority margin. Figure 3 shows the maximum true failure rate in the 3-day treatment group in reference to various possible failure rates in the 5-day treatment group and a 1.5 relative non-inferiority margin (50% relative increase in failure rate) that would result in a 95% confidence interval at maximum enrollment which excludes the non-inferiority margin. The figure also indicates the power the study has to show non-inferiority if the failure rates are exactly the same in the two treatment groups for various possible failure rates. Of note, the estimated power is adjusted for a 5% loss to follow-up rate in each of the arms. This is considered conservative with respect to the multiple imputation procedure that will be used to account for missing outcome values.

**Figure 3.** Chest-indrawing pneumonia failure rates

Note:

- Blue, solid circles, blue number below: Potential failure rates for the 5-day treatment group.

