2. Proportion of children with either treatment failure or clinical relapse before or on day 14 (among all randomized children).
3. Proportion of children with AEs and SAEs.
4. Proportion of children with treatment failure among those testing positive for malaria by rapid diagnostic testing (mRDT) at baseline (overall).
5. Proportion of enrolled children failing treatment among those with wheeze during screening (identified prior to administration of bronchodilators).
6. Proportion of enrolled children failing treatment among those with oxygen saturation <93% by pulse oximetry at baseline.
7. Proportion of children failing treatment among those with MUAC-defined moderate malnutrition (11.5-13.5cm).
8. Proportion of children failing treatment among those with very fast-breathing for age (>70 breaths per minute for 2–11 months, >60 breaths per minute for 12–59 months).
9. Proportion of children failing treatment by age at baseline.
10. **STATISTICAL METHODOLOGY**

*7.1 Design*

The study will include 2,000 children aged 2 to 59 months. Children will be randomized to receive oral amoxicillin for 5 days (control) or 3 days + 2 days placebo (treatment). Treatment will be block randomized (with concealed block size) to ensure a 1:1 ratio of intervention and control. Randomization will be stratified by age group (2 up to 12 months, 12 up to 3 years, 3 years up to 5 years) and site (Bwaila District Hospital and Kamuzu Central Hospital).

*7.2 Interim analysis* We planned two interim analyses after about one-third and two-thirds of children have been enrolled. The seqDesign[2] software was used to determine the appropriate non-inferiority and futility stopping boundaries at each analysis. We assumed a one-sided test with an alpha=0.025, sample size = 1900 (assuming 5% loss to follow-up in each of the arms), a Pocock design for early inferiority and O’Brien-Fleming for early non-inferiority stopping boundaries and a 1.5 relative non-inferiority boundary.

The maximum true failure rates at both the interim analyses and final analysis for the 3-day group for which the 95% CI excludes the non-inferiority margin for various 5-day treatment group failure rates are provided in Table 1 below.

Table 1. Maximum true failure rates for the 3-day treatment arm beyond which stopping for early non-inferiority will be considered

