Hollow, red circles: Maximum true failure rate for the 3-day treatment group observed at maximum enrollment of 2,000 children (1,000 children in each control and treatment groups and assuming 5% loss to follow-up in each of the groups resulting in 1,900 children with complete outcome data for the primary analysis) for which the 95% confidence interval excludes the non-inferiority margin. For example, for a failure rate of 8% in the 5-day treatment group (assumed for the chest-indrawing pneumonia), the true failure rate in the 3-day treatment group can be 9.7% (1.7% above the control group) and can still rule out with high confidence a failure rate of 12% in the 3-day treatment group.

The DSMB will consider recommending to stop the study prior to maximum enrollment if they determine early non-inferiority, early inferiority, or safety concerns.

Early non-inferiority will be considered if the 3-day failure rate is lower than the rates provided in Table 1 for a given 5-day treatment failure rate. For instance, if the 5-day treatment rate at the first interim analysis is 7%, then early non-inferiority will be considered if the 3-day failure rate is less than 4.0%.

Early futility will be considered if the 3-day failure rate is higher than the rates provided in Table 2 for a given 5-day treatment failure rate. For instance, if the 5-day treatment rate at the interim analysis is 7%, then early futility will be considered at the first interim analysis if the 3-day failure rate is higher than 10.2%.

- 1. *Final analysis*

For the primary outcome, we will estimate the failure rate difference and 95% CI between the 3-day and 5-day amoxicillin DT treatment groups after adjustment for age, 2 up to12 months, 12 months up to 3 years, 3 years up to 5 years, site (Bwaila District Hospital and Kamuzu Central Hospital) and gender (precision variable[1]). Since estimates are expressed in rate differences we will run a linear regression model with treatment arm as predictor (3-day vs. 5-day), failure rate (yes vs. no) as outcome and age, site and gender as covariates using robust standard errors and calculate a 95% CI. We will use a 1.5 relative non-inferiority margin. If the failure rate in the 5-day arm is 7%, the non-inferiority margin will be 10.5% (=7%*1.5). With a 5% failure rate the non-inferiority margin will be 7.5% (=5%*1.5).

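### The 9.7% that the plan calls a true 3-day failure rate is a decision boundary for the observed rate; at a true 9.7% against 8% the trial shows non-inferiority only about 41-45% of the time

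*Combined protocol and SAP*

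**What the plan says.** The design assumption is explicit: "We are assuming a treatment failure rate of 8% in the 5-day control group and a relative 1.5 non-inferiority margin". At 8% the margin is therefore 12%, or 4.0 points. The 9.7% figure appears in three places.

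- **Protocol 5.1, Figure 3 notes, and SAP 7.2, Figure 1 notes (same sentence):** the "true failure rate in the 3-day treatment group can be 9.7% (1.7% above the control group) and can still rule out with high confidence" 12% in the 3-day arm. The text introducing each figure also speaks of a maximum true rate.
- **SAP 7.2, Tables 1 and 2:** Table 1 is captioned "Maximum true failure rates for the 3-day treatment arm beyond which stopping for early non-inferiority will be considered", and the Table 2 caption and both lead-in sentences use *true* as well. In the 8% row, Table 1 gives 5.0%, 8.5% and 9.7% at the three analyses. Table 2 gives 11.7%, 10.3% and 9.7%.
- **Protocol 4.5:** the 95% CI would exclude 12.0% "even if the failure rate is as large as 9.7% in the 3-day treatment group". This sentence says neither *true* nor *high confidence*.

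Power is stated only for exactly equal rates in the two arms: 88% at 8%, and from 64.8% at 4% to 96.5% at 12%.

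**The concern.** Four features of the SAP show that the tabulated values are cut-offs for estimates and do not describe underlying rates.

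- The stopping rules after the Figure 1 notes compare the tables with the rates found at an analysis. The worked example takes a 5-day rate of 7% at the first interim.
- The limits move with the look (5.0%, 8.5%, 9.7%). A true rate does not change between analyses.
- The final columns of Tables 1 and 2 are identical in every row. They mark the single point at which success and failure meet.
- The red-circle note describes the same quantity as both true and observed.

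If the true rate sits on such a boundary, the estimate falls on either side about equally often. Because power is otherwise given only for equal rates, this sentence is the plan's only statement about tolerance to a truly worse 3-day arm. It errs in the reassuring direction for the sponsor, the DSMB and the ethics committees.

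**Working it through.** **Inputs.** One-sided alpha 0.025 and 1,900 analysed (SAP 7.2: "We assumed a one-sided test with an alpha=0.025, sample size = 1900 (assuming 5% loss to follow-up in each of the arms"); 950 per arm (Protocol 4.5: "For example, with 1,900 children (950 per treatment arm) for the primary analysis"); control rate 8%; bound 12%; looks at about 1/3, 2/3 and 1; O'Brien-Fleming boundary for non-inferiority and Pocock for inferiority or futility.

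**1. Stated power, fixed-sample approximation.** At 8% in both arms:
- SE = sqrt(2 × 0.08 × 0.92 / 950) = 0.01245.
- Power = Φ(0.04/0.01245 − 1.96) = 89.5%, within 2 points of the stated 88%.

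**2. The printed boundaries.** The documents do not give every design setting. I assumed binding futility, power 0.975 at the design alternative, and variance taken at the control rate and that alternative. Solving gives boundary constants 1.936 and 2.282 (sum 4.218), an alternative of 6.92% and SE 0.01205.
- One non-inferiority step is 1.936 × 0.01205 = 2.33 points. Table 1: 12 − 3 × 2.33 = 5.0; 12 − 1.5 × 2.33 = 8.5; 12 − 2.33 = 9.67.
- One futility step is 2.282 × 0.01205 = 2.75 points. Table 2: 6.92 + 2.75 × √3 = 11.68; 6.92 + 2.75 × √1.5 = 10.29; 6.92 + 2.75 = 9.67.
- Power at equal rates of 4%, 8% and 12% is 64.8%, 88.1% and 96.5%, against the stated 64.8%, 88% and 96.5%.

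The 8% rows and the stated powers reproduce, so 9.7% (9.67% unrounded) is the final boundary on the estimate.

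**3. Success at a true 9.7% against 8%, fixed sample.**
- SE = sqrt((0.08 × 0.92 + 0.097 × 0.903)/950) = 0.01303.
- Power = Φ((0.12 − 0.097)/0.01303 − 1.96) = Φ(−0.19) = 42.3%.

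**4. With the interim looks.** Two million simulated paths were run against the printed 8% rows, with binding futility. A second version used the interim bounds and then an ordinary 95% CI at the final look. The last column ignores futility stops.

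| True 3-day rate | Fixed-sample CI | Printed bounds | Interim bounds, ordinary final CI | Non-binding futility |
| --- | --- | --- | --- | --- |
| 8.0% | 89.5% | 87.4% | 86.3% | about 91% |
| 8.4% | 82% | 80% | 78% | about 84% |
| 9.0% | 65% | 65% | 62% | about 70% |
| 9.7% | 42% | 45% | 41% | about 50% |

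Evaluated at its own final cut-off, each of the six Table 1 rows gives between 41% and 46% under the first three methods. Power of 80% corresponds to a true 3-day rate of about 8.3-8.5%, an excess of about 0.3-0.5 points rather than 1.7.

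**5. Ordinary 95% CI at an observed 9.7% against 8.0%.** The half-width is 1.96 × 0.01303 = 2.55 points. The upper limit is 1.7 + 2.55 = 4.25 points above control, or 12.25%, which does not exclude 12%. The corresponding cut-off would be about 9.5%.

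**The case against.** The strongest reply is that *high confidence* follows a clause about the 95% CI excluding the margin, so it may refer to confidence-interval coverage. That reading would suit an observed 9.7%. It does not rescue a sentence about a true 9.7%, for which the relevant quantity is the chance that the trial succeeds.

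Much else on the other side stands:

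- **No power is claimed at 9.7%.** A reader might infer that the plan promises probable success for an arm truly 1.7 points worse. No such probability is printed; the inference comes from one misplaced word and the phrase that follows it. The *high confidence* sentence is also made only for the 8% example, although the captions label every row as true.
- **Nothing operational changes.** A reader might infer that the boundaries or the sample size are wrong. They reproduce. The DSMB rule compares failure rates at an analysis with the tables, and neither the rule nor the column headings say *true*.
- **Protocol 4.5 does not carry the same wording.** It needs a clarifying word and nothing removed.
- **The power figures depend on assumptions.** The SAP says futility will be considered, so it may not be binding. The SAP also ties the margin to the 5-day rate. With a margin of half the observed control rate, power at true rates of 8.4%, 9.0% and 9.7% is about 76%, 62% and 44%. Testing the 3-day rate minus 1.5 times the 5-day rate gives about 62%, 46% and 28%. No reading brings 9.7% above roughly an even chance.

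**Conclusion.** The point holds as an error of wording and interpretation. The plan labels group-sequential boundaries for the estimated rate as true rates, and so states a tolerance the design does not have. At a true 9.7% against 8%, non-inferiority is shown about 41-45% of the time with a fixed-sample CI or binding futility, and about 50% with non-binding futility. This assumes 950 per arm, a fixed 12% bound and one-sided 0.025. It should be corrected, but it does not threaten the validity of the trial.

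**What to change.** 1. In the Protocol 5.1 text and notes for Figure 3, and in SAP 7.2 (lead-in sentences and captions of Tables 1 and 2, Figure 1 text and notes), replace *true* with *observed (estimated)* wherever it describes the listed 3-day rates.
2. In the same places, state that 9.7% is the final group-sequential boundary and that an ordinary unadjusted 95% CI at an observed 9.7% against 8.0% reaches about 12.25%. Without this qualifier the relabelled text would still be doubtful.
3. Remove *with high confidence*, or reword it so that it does not describe a true rate.
4. In Protocol 4.5, insert *observed* before the 9.7% failure rate and add the same boundary qualifier.
5. Add a power statement with its assumptions, for example: with an 8% control rate, a fixed 12% bound, 950 per arm and one-sided 0.025, power is about 78-82% at a true 3-day rate of 8.4%, 62-65% at 9.0% and 41-45% at 9.7% (fixed-sample CI or binding futility), or about 84%, 70% and 50% with non-binding futility.

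The cost is a few lines of text and a less favourable stated tolerance. Enrolment, boundaries and conduct stay as they are.

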## Missed Visits

In case of a no-show at the clinic for a scheduled study visit, study personnel will call the caregiver and visit the child’s home either that afternoon or the following day to conduct the study visit. Maximum efforts will be made to ensure complete follow-up in the trial. For children who do not complete a scheduled visit within the visit window, that visit will be documented as “missed” but study staff will still attempt to complete the appropriate assessments from that visit, if possible (e.g., Day 6 visit performed and documented on Day 9).

Children who miss a visit, for other than a protocol-mandated reason for discontinuation, are permitted to continue with any subsequent study treatments that can still be scheduled in the time interval specified by the protocol.

Based on our current experience, we expect that fewer than 5% of the children will be lost to follow-up at the time of primary outcome assessment. We think it is unlikely that attrition rates will differ between randomization groups.

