The same treatment failure definition as above will be used for these subgroups analysis. Subgroup classification will be obtained from the screening data.

Additional subgroups not defined in either the approved protocol or statistical analysis plan will be considered post-hoc. Statisticians will keep a list of post-hoc analysis requested by investigators during the study duration.

1. **ENDPOINTS AND COVARIATES**

*6.1 Primary endpoint*

The primary endpoint will be the proportion of children failing treatment, defined as the development of any of the following before or on day 6:

- - - - WHO Integrated Management of Childhood Illness (IMCI) danger signs
      - Severe respiratory distress (e.g., grunting, nasal flaring, head nodding, or severe chest-indrawing).
      - Oxygen saturation < 90% by pulse oximetry
      - Vomiting within 30 minutes of 3 or more scheduled (i.e., not repeat) dose administrations of study product
      - Change in antibiotics prescribed by a study clinician (e.g., switch to a second-line antibiotic or prescription for onset of a co-infection)
      - Death

At or after initial hospitalization discharge assessment (between 42 and 60 hours post-enrollment):

- - - - Documented axillary temperature > 38 ºC with chest-indrawing

At day 6 outcome assessment:

- - - - Documented axillary temperature > 38 ºC
      - Chest-indrawing

The primary endpoint will be calculated from day 2, 4, 6 follow-up forms. The presence of any of the above criteria at any point prior to day 6 will constitute treatment failure. In addition to the overall treatment failure rate by day 6, we will also examine the treatment failure rates at 2 and 4 for both treatment arms.

Covariates for primary analysis: In addition to the treatment variable, the primary analysis will include (be adjusted for) the following covariates: age (2 months up to 12 months, 12 months up to 3 years, 3 years up to 5 years) and site (Bwaila District Hospital and Kamuzu Central Hospital). Of note, these are the same variables that are used for stratifying randomization. In addition, we will adjust for gender, as gender has been shown to be related to pneumonia mortality[1].

*6.2 Secondary endpoints*

The trial has the following several secondary endpoints

1. Proportion of children with clinical relapse between treatment failure assessment and day 14 follow-up visit among all children without treatment failure before or on day 6.

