To account for anticipated loss to follow-up or study withdrawal we will use multiple imputations for any missing outcome data. We will then perform sensitivity analyses to assess how the results might change with varying imputation assumptions. More information is provided in section 8 below.

1. **HANDLING OF MISSING DATA AND OTHER DATA CONVENTIONS**

We have estimated that loss to follow-up or study withdrawal will be 5%. Children lost to follow-up cannot be classified as improved or treatment failures at the missed visit. We will use multiple imputations for any missing outcome data. The imputations will be performed separately for each treatment group and cohort using multiple (20) hotdeck imputations and other information as described below. Multiple imputation estimates will be combined using Rubin’s approach[3].

Specifically, for each episode that is missing outcome data, we will create a subset of episodes that match exactly on treatment arm and gender while matching on age category, highest educational level achieved by the mother (none, primary, secondary, tertiary, while combining these categories for categories with less than 5% of participants, if needed, unknown education level will be multiply imputed, independent from outcome imputation) and adherence information (all combinations of categories for

a) days 1-3: no missing doses, 1-3 missing doses, 4-6 missing doses and

b) days 4-5: no missing doses, 1-2 missing doses, 3-4 missing doses,

unknown dosing information will be conservatively imputed as “not taken” for the 3 day arm and similar to patients where dosing is available for the 5-day arm). We will then randomly select one episode from the corresponding subset with complete information and use its values to replace the entire episode with missing outcome data.

We will repeat this process for each episode missing outcome data and calculate failure rates for both treatment arms using the imputed outcome. We will repeat this 20 times and determine the mean failure rates for each treatment arm. The difference between the mean failure rates will be calculated. Noninferiority bounds as listed in 7.2 will be consulted.

1. **SENSITIVITY ANALYSIS**

We will perform sensitivity analyses to assess how our results might change if the imputation assumptions are changed in a reasonable way, informing the robustness of the primary analysis result. We will perform complete case analysis as one form of sensitivity analysis.

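### SAP section 8 imputes without using the lost child's observed clinical status, so a child seen failure-free on Day 4 can be imputed as an early failure; the effect is small and leans towards non-inferiority

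*Combined protocol and SAP*

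**What the plan says.** SAP section 8 (Handling of Missing Data) states the imputation in three steps.

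- **Matching:** "for each episode that is missing outcome data, we will create a subset of episodes that match exactly on treatment arm and gender". Age category, mother's education and adherence in two periods (days 1-3 and days 4-5) are also matched.
- **Draw:** the analyst will "randomly select one episode from the corresponding subset with complete information".
- **Replacement:** the analyst will "use its values to replace the entire episode with missing outcome data". This is repeated 20 times.

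Clinical status at the last completed visit is not a matching variable, and children who failed early are not barred as donors.

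SAP 6.1 builds the primary endpoint from the Day 2, 4 and 6 forms and adds: "The presence of any of the above criteria at any point prior to day 6 will constitute treatment failure". Protocol 4.6 has every child examined on Day 2 in hospital, at the discharge assessment and on Day 4. SAP section 9 names complete-case analysis as one sensitivity analysis. It refers to other changes of the imputation assumptions without saying what they are.

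**The concern.** A child lost between Day 4 and day 6 is only partly unobserved. The record already shows that none of the failure criteria applicable up to Day 4 had been met. What is missing is the short period to day 6. The rule treats such a child as if nothing were known after baseline except dosing, and gives the child the failure risk of the whole period.

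Two things follow. An imputed record can contradict a recorded finding. The imputed risk is also too high for every child lost while still well, so the error runs in one direction.

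Both arms take active drug through Day 3, so early failures assigned to children known to have passed that stage carry no information about duration. They still raise the control rate, and the non-inferiority margin is 1.5 times that rate.

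**Working it through.** **Inputs from the documents.** 1,000 children per arm, 5% loss (50 per arm, 950 analysed), 8% control failure, relative margin 1.5 (4.0 points at 8%), one-sided alpha 0.025, stated power 88%.

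**Inputs assumed.** The share of failures occurring by Day 4 and the timing of losses are not given. The main case takes e = 4 to 6 of the 8 points by Day 4, the same in both arms, with all losses after Day 4 among children still well. The arithmetic ignores covariate and adherence matching.

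**1. The plan's own figure.** Standard error = √(2 × 0.08 × 0.92 / 950) = 0.01245. Then 0.04 / 0.01245 − 1.96 = 1.25, which gives fixed-sample power of 89.5%. Simulating the three looks with the 8% rows of SAP Tables 1 and 2 gives 87.6%. The stated 88% is reproduced.

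**2. Remaining risk for a child well on Day 4** = (0.08 − e) / (1 − e).
- e = 0.04: 0.04 / 0.96 = 4.2%
- e = 0.06: 0.02 / 0.94 = 2.1%

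An unrestricted donor fails with probability about 8%, two to four times too high.

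**3. Shift in one arm's rate** = 0.05 × (0.08 − remaining risk).
- e = 0.04: 0.05 × (0.08 − 0.0417) = 0.19 points
- e = 0.06: 0.05 × (0.08 − 0.0213) = 0.29 points

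If the share of failures by Day 4 runs from 25% to 90%, the shift is 0.09 to 0.36 points, with a ceiling of 0.05 × 0.08 = 0.40. If only half the losses fall after Day 4, these figures halve.

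**4. Effect on the comparison.** Non-inferiority turns on p3 − 1.5 × p5. If both arms rise by s, this moves by s − 1.5s = −0.5s.
- s = 0.19: −0.10 points
- s = 0.29: −0.15 points

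The sign favours non-inferiority. Over the wider range in step 3 the move is 0.05 to 0.18 points.

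**5. The same at the margin** (3-day rate 12%, same e in both arms). For e = 0.04 the remaining risk in the 3-day arm is 0.08 / 0.96 = 8.33% and its shift is 0.05 × (0.12 − 0.0833) = 0.18 points. The net move is 0.18 − 1.5 × 0.19 = −0.10 points. So the lean is also present where a false claim of non-inferiority would arise. If early failures were instead also 1.5 times as frequent in the 3-day arm, the shift there is 0.281 points against 1.5 × 0.192 = 0.288, and almost nothing remains.

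**6. What complete-case analysis shows.** Per 1,000 with e = 0.04: 40 early failures, 960 still well, 50 of them lost, and 910 × 0.0417 = 37.9 later failures. The complete-case rate is 77.9 / 950 = 8.2%, against a true 8.0%. It has the same upward bias as the unrestricted draw, so agreement between the two would not be reassurance. With restricted donors the 50 lost children contribute 50 × 0.0417 = 2.1 failures, and (77.9 + 2.1) / 1,000 = 8.0%.

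**7. Unequal loss.** If the 0.19 points fell on the 3-day arm alone, fixed-sample power would go from 89.5% to about 86.5%.

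**The case against.** The strongest reply is that the effect is minor. The same procedure runs in both arms, the protocol (4.6, Missed Visits) expects no difference in attrition, and the 95% half-width at 8% with 950 per arm is 1.96 × 0.01245 = 2.4 points. A net 0.10 to 0.15 points is small beside that. This stands, and it sets the size of the point. It does not defend the rule, which discards information already collected.

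A second reply is that adherence matching may change the donor pool. Pill counts are taken at Day 6, so a child lost after Day 4 will often lack full days 4-5 dosing. The unknown-dosing rule then applies: not taken in the 3-day arm, and otherwise "for the 3 day arm and similar to patients where dosing is available for the 5-day arm". This is fair, and it makes the figures above approximate. It does not remove the problem: adherence is not clinical status, and the documents do not say how doses stopped after a failure are counted.

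Third, SAP section 9 promises other imputation assumptions. None is specified, and the one analysis named shares the bias.

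Three stronger readings are tempting, and the documents do not support them.

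- **Known failures redrawn as cures.** A reader might infer this from the protocol (5.1, Objectives and Endpoints): "Loss to follow-up or withdrawal from the study at any time after enrollment and before the day 14 follow-up visit will be considered missing outcome". That sentence goes on to limit missingness to the time point concerned. SAP 6.1 makes any criterion met before day 6 a failure, so the primary outcome of such a child is known and the episode is not one to impute.
- **A day-14 composite below the primary failures it contains.** The composite in SAP 6.2 is "Proportion of children with either treatment failure or clinical relapse before or on day 14 (among all randomized children". A recorded failure settles it, whatever happens later.
- **Late Day 6 findings thrown away.** Protocol 4.6 says "that visit will be documented as “missed” but study staff will still attempt to complete the appropriate assessments from that visit". The SAP is silent on how a late finding is used, but nothing says that it is discarded or replaced by a draw.

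**Conclusion.** The point holds for one group: children recorded as failure-free at a completed visit and then lost before day 6. Their imputed failure risk is about 8% where 4.2% to 2.1% would be right, which adds 0.2 to 0.3 points to each arm. With similar loss in both arms, a lean of about 0.10 to 0.15 points towards non-inferiority remains, against a 4.0-point margin.

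This rests on 8% failure, 5% loss all after Day 4, and 4 to 6 points of failure by Day 4 in both arms. The last two are assumptions. The effect alone is unlikely to change the trial's conclusion. It is still worth correcting, because it leans towards the claim being tested, the named sensitivity analysis cannot show it, and the correction costs almost nothing. For recorded failures, all that is lacking is an explicit sentence saying that they stand. The existing definitions already point that way.

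**What to change.** In SAP section 8, replace the sentence on replacing the whole episode by: *Data observed before loss are kept. Donors are restricted to children in the same arm (and matching cell) still failure-free at the lost child's last completed assessment, and only later assessments are taken from the donor.*

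As a clarification consistent with SAP 6.1, SAP 6.2 and protocol 5.1, add: *A failure recorded on or before day 6 is final for the primary endpoint and for the day-14 composite.*

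The cost is this wording and one filter in the R code. Donor pools lose the children who had already failed by that visit, about 40 to 60 per 1,000 under the assumptions above. Visits, data collection and sample size do not change.
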